# The clinical and cost effectiveness of a conservative treatment pathway compared to appendicectomy in children with uncomplicated acute appendicitis: study protocol for a randomised controlled multi-centre open-label parallel-group non-inferiority trial (CONTRACT 2 trial) in the United Kingdom (UK)

**DOI:** 10.1186/s13063-025-09282-y

**Published:** 2025-12-04

**Keywords:** Appendicitis, Appendicectomy, Non-operative treatment, Abdominal pain, Paediatric surgery, Randomised controlled trial, Non-inferiority, Evidence-based medicine, Qualitative research, Economic evaluation

## Abstract

**Background:**

Currently, the most frequently used treatment for acute appendicitis in children in the United Kingdom (UK) is an appendicectomy. However, there is increasing scientific and patient interest and research into non-operative treatment of appendicitis. Despite a number of non-randomised studies in children and randomised studies in adults, comparative outcomes of non-operative treatment and appendicectomy in comparable groups of children remain unknown. Following the successful completion of a feasibility study, we now aim to perform a UK-based multi-centre open-label randomised controlled trial (RCT) to investigate the clinical and cost-effectiveness of non-operative treatment pathway of acute uncomplicated appendicitis in children compared with appendicectomy.

**Methods:**

Non-inferiority RCT with internal pilot, health economic evaluation and qualitative communication sub-study. The study is conducted in England, Northern Ireland, Scotland and Wales at both specialist children’s hospitals and district general hospitals. Children (aged 4–15 years inclusive) diagnosed with acute uncomplicated appendicitis that would normally be treated with an appendicectomy are eligible for the RCT. Exclusion criteria include clinical/radiological suspicion of perforated appendicitis, appendix mass or previous non-operative treatment of appendicitis. Sample size is 376 participants, recruited by surgeons and supported by research staff and randomised with a 1:1 allocation ratio to either non-operative treatment pathway (intervention) or appendicectomy (control). Participants in the intervention arm are treated with antibiotics, analgesia and regular clinical assessment to ensure clinical improvement. Participants in the control arm receive appendicectomy. Randomisation is minimised by age, sex, duration of symptoms and centre. The primary end-point is a composite outcome of treatment success at 1 year following randomisation. Secondary outcomes include: duration of hospital stay, measures of recovery from acute appendicitis, complications, need for further treatment, persistent symptoms, health care resource use, quality of life and costs. Adverse events, serious adverse events and suspected unexpected serious adverse events are collected directly on the database and by paper form up to 12-month visit. Primary outcome will be analysed on a non-inferiority basis using a 20% non-inferiority margin to test the hypothesis that non-operative treatment pathway is non-inferior to appendicectomy. Children and families who are approached for the RCT will be invited to participate in the embedded qualitative sub-study. This will include recording of recruitment consultations, which will inform future interventions to optimise recruitment. We have involved children, young people and parents in study design and delivery.

**Discussion:**

This RCT will allow determination of the comparative clinical and cost-effectiveness of non-operative treatment pathway compared to appendicectomy for children with uncomplicated acute appendicitis in the UK.

**Trial status:**

First planned enrolment—December 2022, first actual recruit—March 2022, current status of trial—open to recruitment.

**Trial registration:**

ISRCTN16720026. Registered on July 28, 2021.

## Introduction

### Background and rationale {6a}

Acute appendicitis is the most common surgical emergency in children [1]. The lifetime risk is 7–8% with a peak incidence in the early teens [2, 3]. Appendicectomy is considered the gold standard treatment by most surgeons. In 2023–2024, there were 7408 emergency appendicectomies in England in children aged < 16 years old [4]. Due to this volume, management of children with appendicitis incurs significant costs for the healthcare service each year [5].

For parents, the need for emergency surgery is frightening and many are keen to avoid surgery if an alternative is available. Surgeons are frequently asked ‘Does my child really need an operation?’ Whilst appendicectomy is generally safe, it involves a general anaesthetic and an abdominal operation with inherent risks and potential complications. Work we have undertaken with parents shows that over 80% would be willing to consider non-operative treatment pathway for their child with appendicitis, and 60% would prefer non-operative treatment to surgery if outcomes were similar (20% preferred surgery and 20% expressed no-preference) [6].

An alternative would be to treat children non-operatively, without surgery but with antibiotics. This would have the benefit of avoiding an operation and potential side effects but would only be acceptable if antibiotic treatment has a high success rate and the risk of serious complications and recurrent appendicitis is low. Although research to date has confirmed that most children with uncomplicated acute appendicitis can be successfully treated without surgery [7–12], there have been no adequately powered randomised controlled trials (RCTs) reported before the start of CONTRACT 2 that directly compare these two very different treatments and conduct an economic evaluation. Comparative data are needed to help inform future practice and, in particular, to inform treatment choices by children, parents, clinicians, National Health Service (NHS) commissioners and healthcare policy makers.

Anticipating challenges in recruiting to such an RCT, we have already successfully performed a detailed feasibility study with embedded qualitative research and work to inform a health economic analysis [5, 13–19]. From this, we have confirmed that we can recruit participants to an RCT, gained valuable insights to optimise trial recruitment and retention, confirmed the safety of a non-operative treatment pathway in a UK setting, determined outcomes of importance to measure, discussed the acceptable non-inferiority margin with clinicians, patients and parents [13, 16, 19] and determined cost-drivers to underpin the design of a full economic analysis [5, 15]. We now plan to perform a large multi-centre non-inferiority RCT, generating the evidence to inform future clinical practice in the UK.

### Objectives {7}

Primary: To determine whether a non-operative treatment pathway is non-inferior to appendicectomy for the treatment of children with uncomplicated acute appendicitis. The primary outcome of ‘treatment success’ will be assessed at 1 year following randomisation.

Secondary: To compare a non-operative treatment pathway with appendicectomy in terms of other important patient- and family-centred outcomes and cost. Outcomes will include duration of hospital stay, measures of recovery from acute appendicitis, complications, need for further treatment, persistent symptoms, health care resource use, quality of life and costs. We will measure all applicable outcomes in our developed core outcome set [13, 19].

### Trial design {8}

A multi-centre, open-label, parallel-group, non-inferiority randomised controlled trial comparing a non-operative treatment pathway with appendicectomy with internal pilot, health economic evaluation and qualitative sub-study. Both groups of children will receive broad spectrum antibiotics from the point of diagnosis; one group of children will undergo urgent appendicectomy, the other will be treated non-operatively with continuation of broad spectrum intravenous antibiotics. Patients enrolled in the study will be randomised at a ratio of 1:1. See Fig. 1 for a Trial schema overview.

**Fig. 1 Fig1:**
[figure not shown]
Trial schema

#### Internal pilot stage

The pilot stage is embedded in this RCT to ensure that recruitment outside of the three sites used in our feasibility study is possible, confirm our anticipated recruitment rate, implement recruiter training and adjust the overall trial profile if necessary. We have devised a comprehensive program of recruiter training and re-training, using an evidence-based approach with some limited qualitative work and informed by our feasibility study [5, 13–19], which we believe is crucial to achieving target recruitment.

We have focused pilot stage metrics on actual recruitment, which is dependent on initiating sites and successfully recruiting participants. In our feasibility study [5, 13–19], we successfully opened all three sites on the same day, whilst in CONTRACT 2 we stagger site opening and aim to open all sites within the first 6 months of recruitment.

Internal pilot data will be analysed after 12 months from the start of recruitment to assess trial and recruitment progress. The decision of progression to full trial will be taken by the Trial Steering Committee (TSC) in conjunction with the funder, based on traffic light criteria assessed after 12 months of recruitment (Table 1).

**Table 1 Tab1:** Traffic light criteria for the pilot phase assessed after 12 months of recruitment

Pilot phase criteria	Red	Amber	Green
% Threshold (of participants)	<75%	75-99%	100%
Total number of participants recruited	<120	120-159	≥160
Number of sited opened	<7	7-9	≥10

Note: Green - immediate progression to full RCT; Amber - prolongation of pilot phase for further 6 months to allow further identification of sites and/or further training at existing sites; Red - undertake urgent detailed review of options with TSC and report to HTA

All data from the internal pilot and subsequent RCT will be used in the final analysis. No interim analysis of effectiveness is planned. Data will be presented according to the Consolidated Standards of Reporting Trials (CONSORT) guidelines extension for non-inferiority trials, 2012 [20].

## Methods: participants, interventions and outcomes

### Study setting {9}

Specialist Paediatric Surgical Units and General Hospitals in the UK.

### Eligibility criteria {10}

Eligible participants will be identified by the clinical team at time of diagnosis of acute appendicitis.

**Inclusion criteria**:Children aged 4–15 yearsClinical diagnosis, with or without radiological assessment, of acute appendicitis which prior to study commencement would be treated with appendicectomyWritten informed parental or guardian consent, with child assent if appropriate

**Exclusion criteria**:Complicated appendicitis score (Table 2) of 4 or greaterClinical or Radiological findings to suggest perforated appendicitisPresentation with appendix massPrevious episode of appendicitis or appendix mass treated non-operativelyMajor anaesthetic risk precluding allocation to the appendicectomy armDocumented allergy to first and second line broad spectrum antibiotics preventing allocation to non-operative treatment armPositive pregnancy test (only required for female patients of child bearing potential)

**Table 2 Tab2:** Complicated appendicitis score

Parameter	Points
Rebound tenderness	1
Duration of pain ≥ 48 h	1
Temperature* ≥ 37.5 °C	1
Neutrophil count ≥ 11 (× 10^9^/L)	2
CRP ≥ 50 (mg/L)	2

*Documented temperature, in hospital, at any stage prior to diagnosis; *CRP* - C-reactive protein

Note: The complicated appendicitis score was developed following feedback from surgeons during our feasibility study [5, 13–19] indicating that a more objective means of distinguishing between children with uncomplicated appendicitis and those with more advanced disease was necessary

### Who will take informed consent? {26a}

Recruitment discussions will be conducted by the clinical team with responsibility for the patient, and consent will be taken by clinical teams or research nurses.

### Additional consent provisions for collection and use of participant data and biological specimens {26b}

We will seek consent from parents to contact them at yearly intervals by telephone/e-mail for longer term follow-up, up to a maximum of 5 years. We will request consent to store personal data (telephone number and e-mail address) securely for the purposes of this RCT only. We will also seek consent to use a patient identifier for the purposes of recording long term outcomes from national datasets of routinely collected data. These activities are outside of the current funding remit.

## Interventions

### Explanation for the choice of comparators {6b}

Currently, the most frequently used treatment for children with appendicitis in the UK is appendicectomy. There is increasing interest and demand for non-operative treatment of uncomplicated appendicitis in children but a lack of data comparing non-operative treatment pathway with appendicectomy. Comparative data are required to inform clinical practice and shared decision making.

### Intervention description {11a}

#### Non-operative treatment group

This treatment pathway will comprise (i) fluid resuscitation, (ii) a minimum of 24-h intravenous antibiotics (determined by local hospital standard antibiotics for appendicitis, as per our feasibility study), (iii) analgesia and (iv) regular clinical review to detect symptoms and signs of significant clinical deterioration including, but not limited to, increasing fever, increasing tachycardia and increasing pain/tenderness. In our feasibility study [5, 13–19], we recommended a minimum period of being ‘nil-by-mouth’ but learnt from experience that this was unnecessary and deterred some children from participating, therefore this requirement has been removed for this RCT.

Once children have received minimum 24-h intravenous antibiotics, have been afebrile for 24 h and are tolerating oral intake, they will be converted to oral antibiotics (co-amoxiclav as per standard practice). Once discharge criteria are met (see below), they will be discharged. In total, children in the intervention group will receive a course of 10 days antibiotics following randomisation. Children who receive non-operative treatment will not be offered appendicectomy, but they and their parents will be counselled about the risk of recurrence and appropriate action to take. Children who require appendicectomy for failure of non-operative treatment during the initial admission will be treated post-operatively according to a standardised treatment regime already in use at participating institutions, and identical to that to be used in children in the appendicectomy group.

#### Appendicectomy group

Children allocated to appendicectomy group will undergo urgent appendicectomy according to current treatment pathways at participating centres. The procedure may be performed by a suitably experienced trainee (as is routine current practice) or a consultant. The procedure may be performed open or laparoscopically at the discretion of the clinical team according to their current practice (in our feasibility study, open appendicectomy was a rare event).

It is recommended to take a peritoneal microbiology swab at the time the peritoneum is first opened and any peritoneal fluid sent for microbiological culture. Participants will receive intravenous antibiotics from the time of randomisation and be treated post-operatively with intravenous antibiotics (according to existing treatment pathways already in use at participating centres). Typically, children with uncomplicated acute appendicitis or a macroscopically normal appendix will receive no further antibiotics. If unexpectedly a perforated appendix is discovered at surgery (defined as a faecalith or faecal matter within the peritoneal cavity or visualisation of a hole in the appendix) [21], then intravenous antibiotics will be continued for a minimum of 3 days, with a minimum total course of antibiotics of 5 days (intravenous and oral). It is not possible to completely ‘protocolise’ the duration of antibiotic therapy due to anticipated variation in response to treatment. Children with perforated appendix will remain in the RCT.

The type of antibiotics initially used will be according to current standard local hospital policy. Any child failing to respond to these first line antibiotics will be treated as is clinically appropriate with a longer course of antibiotics, or a change in antibiotic therapy with choice of antibiotic determined by intra-operative swab or fluid culture. Post-operatively, children with uncomplicated acute appendicitis or a normal appendix will not routinely have a nasogastric tube, nor a urinary catheter; they will receive oral intake as tolerated after surgery.

#### Discharge from hospital

The decision to discharge the child home will be made by the clinical team using standard clinical criteria for both treatment groups which will be (i) afebrile, (ii) vital signs within normal limits, (iii) able to tolerate oral intake and (iv) able to mobilise. The time the decision to discharge was made and the time of actual discharge will be recorded. Prior to discharge, parents will be assisted to download a smartphone app to allow daily data collection directly from parents during the first 4 weeks following hospital discharge. A paper patient diary card can be supplied for those without access to a smartphone.

All participants, across both treatment groups, will be provided with a discharge pack. This pack will contain a leaflet highlighting concerning symptoms and action to be taken should any of them occur, including advice to contact a member of the medical team at each participating hospital (with relevant contact details), or the participant’s GP in an emergency and the telephone number of the research nursing team at each site for less urgent concerns. We will write to the participant’s GP to inform them of their patient’s inclusion in the RCT.

### Criteria for discontinuing or modifying allocated interventions {11b}

Children receiving non-operative treatment who, in the opinion of the consultant surgeon in charge of their care, have clinically deteriorated such that immediate appendicectomy is mandated, will undergo appendicectomy at any stage. A formal review will be performed at 24 h following randomisation, and any child deemed to have significantly deteriorated (e.g. deterioration in objective clinical observations which in the view of the surgeon in charge of their care justifies urgent appendicectomy) will undergo appendicectomy. Those who are stable or clinically improving will continue with non-operative treatment. Those who are not showing clinical signs of improvement at 48 h following randomisation will undergo appendicectomy. This decision will be made based on the clinical judgement of the treating consultant as is current practice rather than on any predefined set of criteria for which evidence does not currently exist. These decision points are included in the non-operative treatment pathway and therefore these patients will have been considered to have received their allocated intervention.

### Strategies to improve adherence to interventions {11c}

Both interventions are routine clinical interventions in the acute care setting. We do not therefore anticipate significant challenges with adherence but will monitor and address this through site training if necessary. Site staff will check the database regularly and contact any patients who have not provided follow-up data as a prompt to complete.

### Relevant concomitant care permitted or prohibited during the trial {11d}

None for this trial.

### Provisions for post-trial care {30}

All participants will be followed up for 1 year following randomisation. Formal follow-up appointments will take place at 6 weeks, 4 months, 8 months and 12 months following randomisation. The 6-week follow-up appointment will take place in the outpatient clinic or Clinical Research Facility at each participating centre (can be also completed via a phone call in case of patient’s unavailability for an in-person appointment, e.g. due to Covid). The 4-, 8- and 12-month appointments should be completed over the phone or video call. The follow-up appointments should be completed no earlier than 1 week before the projected visit date, and no later than 2 weeks after the projected visit date.

Data will be collected during these follow-up visits to ensure high accuracy. These visits will ensure completeness of the dataset collected, in particular time to return to daily activities, recurrent appendix-related problems (including unexplained abdominal pain and recurrence) and resource use data. If the visit is missed, a nurse will access the patient’s hospital records to obtain necessary information for the primary outcome of this RCT: any re-admissions and/or complications since the last visit.

Children treated non-operatively who present with suspected recurrent appendicitis during the 1-year follow-up period will not be eligible for re-randomisation. These cases will be recorded in this RCT as a failure of non-operative treatment pathway. These cases are typically treated with appendicectomy and not treated non-operatively, unless re-presentation is with appendix mass or abscess and non-operative treatment is felt preferable by the clinical team.

Children treated with appendicectomy who present with a complication related to their initial procedure shall be treated as deemed clinically appropriate by the clinical team.

### Outcomes {12}

Primary outcome is treatment success (binary variable ‘yes/no’), to be measured at 1 year following randomisation and defined as recovery from acute appendicitis and having none of the following: (i) negative appendicectomy (no histological evidence of inflammation), (ii) complication requiring intervention under general anaesthesia, (iii) failure of non-operative treatment pathway during initial hospital admission (treated with appendicectomy) and (iv) recurrent appendicitis (based on histological assessment or further episode of non-operative treatment if appendicectomy not performed). Secondary outcomes and measurement timepoints are listed in Table 3 below.

**Table 3 Tab3:** Secondary outcomes

Outcome (Y/N, otherwise stated)	Timing of measurement	Method of measurement
Negative appendicectomy*^$^	Hospital discharge, 6-week review	Research nurse
Intra-abdominal abscess*	Hospital discharge, 6-week review	Research nurse
Reoperation*^$^	Hospital discharge, 6-week, 4-, 8-, 12-month	Research nurse
Bowel obstruction*	Hospital discharge, 6-week, 4-, 8-, 12- month	Research nurse
Wound infection*	Hospital discharge, 6-week review	Research nurse
Other wound complication*	Hospital discharge, 6-week review	Research nurse
Antibiotic failure*^$^	Hospital discharge, 6-week review	Research nurse
Length of hospital stay* [days]	Hospital discharge, 6-week, 4-, 8-, 12-month	Research nurse
Histology of appendix^1^	Hospital discharge, 6-week, 4-, 8-, 12-month	Research nurse
Adverse events*	Hospital discharge, 6-week, 4-, 8-, 12-month	Research nurse
Recurrent appendicitis*^$+^	6-week and 4-, 8-, 12-month	Research nurse
Readmission to hospital*	6-week and 4-, 8-, 12-month	Research nurse
Appendicectomy without recurrent appendicitis on histology	6-week and 4-, 8-, 12-month	Research nurse
Caregiver and patient’s quality of life* (CHU-9D)^2^	At randomisation, week 1–4, week 6 and 4-, 8-, 12-month	Research Nurse (option of smartphone app at weeks 1–4)
Healthcare resource use (shortened CSRI)^3^	6-week and 4-, 8-, 12-month	Research nurse
Death*	Hospital discharge, 6-week and 4-, 8-, 12-month	Research nurse
Pain meds taken for appendicitis	Hospital Discharge, then daily for 3 weeks	Smartphone app/paper card
Able to do normal daily activities	Hospital Discharge, then daily for 3 weeks	Smartphone app/paper card
Attended school (if applicable)	Hospital Discharge, then daily for 3 weeks	Smartphone app/paper card
Able to do full activities*	Hospital Discharge, then daily for 3 weeks	Smartphone app/paper card
Parent/main caregiver missed work	Hospital Discharge, then daily for 3 weeks	Smartphone app/paper card

*Indicates outcome within core outcome set

$ Indicates part of composite primary outcome

^+^Recurrent appendicitis is defined as symptom recurrence followed by EITHER appendicectomy with histological confirmation of acute appendicitis OR a clinician diagnosis of appendicitis with appendix mass or abscess treated non-operatively; appendicectomy without histological confirmation of acute appendicitis is a separate secondary outcome

^1^Histology of appendix consists of the next categories: (1) not applicable, (2) no abnormality, (3) simple acute appendicitis, (4) perforated, (5) Enterobius detected, (6) other

^2^For the purposes of economic evaluations, a utility score (ranging from 0 to 1, with 1 being perfect health) is calculated as the sum of the scores for each of nine dimensions of the CHU-9D questionnaire (worry, sadness, pain, tiredness, annoyance, schoolwork/homework, sleep, daily routine and ability to join in activities)

^3^A short modified version of the CSRI (Client Service Resource Inventory) questionnaire collects the information in the last 6 weeks on: (1) health and social care service use (the number of hospital stays, visits to a health care professionals and the types of health services), (2) family born costs (expenses related to child’s appendicitis, e.g., travel to hospital, painkillers, heat or massage oils, herbal or complimentary remedies), (3) parent’s, carer’s, partner’s employment loss and child’s absent from school (if yes, number of days)

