### Data collection and health economic outcomes

#### Resource use, costs and HRQoL data

In accordance with findings of our feasibility study [5, 13–19], the primary care data from parents will be collected by research nurses during phone calls and in person interviews using a short modified version of the CSRI (Client Service Resource Inventory) questionnaire [25–27]. For secondary care data, we will use the Patient Level Information and Costing Systems (PLICS) [28] data for acute services records activity and cost information for admitted patient care, outpatient appointments and A&E attendances. The results from our feasibility study support the use of PLICS data as a reliable alternative to micro-costing [5]. Unit cost will use the NHS Reference Costs [29] and Personal Social Services Research Unit (PSSRU) [30] data in addition to other unit costs as appropriate. To allow reporting in QALY terms, we will use the caregiver-reported CHU-9D.

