#### Timing of health economic data collection

The data collection refers to hospital records for admission(s) to hospital(s) up to 12-month duration, including admissions for recurrent appendicitis and/or other related admissions. Data regarding health care resource use will be collected directly from parents/guardians through a smartphone app weekly up to 4 weeks following randomisation. These records will be discussed in detail during a face-to-face visit at 6 weeks. Health economics (HE) data will be collected during phone calls at 4-, 8- and 12-month visits, and the e-CSRI questionnaire will be completed by a research nurse during these visits at 6 weeks and 4, 8 and 12 months.

Our previous work revealed that timing is an important consideration for collecting QoL data and estimating QALYs for this intervention. While there was a significant difference in QoL at 2 weeks, this difference was not present at 6 weeks, by which time both groups had returned to almost full health. Therefore, we will record QoL data at baseline, weekly up to 4 weeks and then at 6 weeks, in order to identify the return to full health and normal life for children in both arms. The CUA will report these short-term outcomes in QALYs.

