#### Health economic analysis

Overall, the economic evaluation will report the long-term results from the CEA at 1 year using the primary outcome, reporting cost per successfully treated child. The CUA will report the short to medium-term cost per QALY gained at 6 weeks, when full recovery for both arms is expected. Extending the time to 1 year risks diluting the actual difference between the two treatment arms in QALY terms, and it is important to show the short-term implication in QALY terms. However, sensitivity analysis will explore long-term implications by incorporating recurrence of appendicitis, both in terms of increased costs and reduced QALYS. The potential of bias will also be explored using sensitivity analysis if increased cross-over between arms is observed. As part of the economic analysis, we will also report the economic implications for the NHS in terms of defining tariff for the non-operative treatment option and reporting on the economic impact this might have to the NHS. We will develop a full Health Economics Analysis Plan.

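### A 6-week CSRI recall, given at 6 weeks and 4, 8 and 12 months, leaves 28 of 52 weeks of primary and community care unobserved in the 1-year cost analysis

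*Protocol article*

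**What the plan says.** Outcomes {12}, Table 3, lists healthcare resource use by shortened CSRI at 6 weeks and 4, 8 and 12 months. Footnote 3 to that row says the "questionnaire collects the information in the last 6 weeks on: (1) health and social care service use". The same footnote places family items in the form: "family born costs (expenses related to child’s appendicitis, e.g., travel to hospital, painkillers, heat or massage oils, herbal or complimentary remedies", together with carers' employment loss and the child's absence from school.

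Timing of health economic data collection repeats the schedule: "the e-CSRI questionnaire will be completed by a research nurse during these visits at 6 weeks and 4, 8 and 12 months". Table 4 ticks the same four visits. Resource use, costs and HRQoL data gives the form its role: "the primary care data from parents will be collected by research nurses during phone calls and in person interviews", with the shortened CSRI as the instrument. Hospital care comes from PLICS (admitted care, outpatient appointments, A&E) and from hospital records up to 12 months.

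On the horizon, Health economic analysis states that "the economic evaluation will report the long-term results from the CEA at 1 year using the primary outcome, reporting cost per successfully treated child". Follow-up matches: "All participants will be followed up for 1 year following randomisation". Provisions for post-trial care {30} says that the follow-up visits make the dataset complete, and names resource use data. The economic perspective is the NHS.

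**The concern.** A 6-week recall fits the 6-week visit exactly and none of the later ones. If the later forms also look back only 6 weeks, each leaves a stretch since the previous contact about which nobody is asked. The article names no other source for GP and community contacts in those stretches: PLICS is hospital data, and the weekly app contact data stop at week 4.

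Two things are at stake. The stated completeness of resource use data would not be met, and a 1-year cost per successfully treated child would rest on primary-care data from less than half the year. If the uncovered weeks were then added up as nil, primary-care cost after week 6 would be too low. The shortfall could differ by arm: recurrence belongs to the non-operative pathway and arises over the following months, whereas the article expects both groups to be close to full health by 6 weeks.

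**Working it through.** The article gives no coverage figure, so there is none to reproduce. Coverage is computed as the union of the intervals from (visit − 6 weeks) to the visit.

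**Inputs**
- Recall: 6 weeks (Table 3, footnote 3).
- Visits: 6 weeks, 4, 8 and 12 months (Tables 3 and 4; Timing of health economic data collection).
- Visit window: −1 to +2 weeks (Provisions for post-trial care {30}; Table 4).
- App resource-use data: weekly to week 4.
- Horizon: 1 year, taken as 52 weeks.
- Conversion: 1 month = 365.25/12/7 = 4.35 weeks, so the later visits fall at weeks 17.4, 34.8 and about 52.

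**Coverage at the nominal dates**

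| Visit | Weeks since previous visit | Weeks covered | Gap before the covered window |
|---|---|---|---|
| 6 weeks | 6 | 0 to 6 | 0 |
| 4 months | 11.4 | 11.4 to 17.4 | 5.4 |
| 8 months | 17.4 | 28.8 to 34.8 | 11.4 |
| 12 months | about 17.4 | 46 to 52 | about 11.3 |

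- The windows do not overlap. Covered: 4 × 6 = 24 weeks; 24/52 = 46%.
- Uncovered: 52 − 24 = 28 weeks; 28/52 = 54%.
- After week 6: 3 × 6 = 18 of 46 weeks covered (39%); 28 of 46 uncovered (61%).
- The app's weeks 0 to 4 lie inside the first window and add nothing at nominal dates.

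**Across the permitted visit windows**
- Least coverage: the first visit a week early covers 5 weeks, and the 12-month visit two weeks late has only 4 of its 6 weeks inside the year. 5 + 6 + 6 + 4 = 21 weeks, leaving 31.
- Most coverage: the first visit two weeks late covers weeks 2 to 8, and the app supplies weeks 0 to 2. 8 + 6 + 6 + 6 = 26 weeks, leaving 26.

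**With recall matched to the interval**
- 6 + 11.4 + 17.4 + 17.4 = 52 weeks to rounding, so the gap is 0.

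**What each gap touches**
- Admissions, outpatient and A&E care: covered to 12 months by PLICS and hospital records.
- GP and other community contacts after week 6: subject to the 28-week gap, and inside the NHS perspective.
- Family costs, school absence, lost work: subject to the same gap, but outside the NHS perspective, so they do not enter cost per success.
- Cost-utility analysis at 6 weeks: fully inside the first window.

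**The case against.** The case on the other side has four parts.

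**The evidence is one phrase in a footnote of a condensed article.** The form itself is not shown, and the phrase may describe only the 6-week version. Table 4 has a separate resource-use row ticked at the later visits, and the timing section mentions health economic data by phone as well as the e-CSRI. This stands as a limit: a reader might infer that the data are certainly lost, and the article does not establish that. But the footnote is attached to a row with all four timepoints, and no other primary-care instrument or recall period is named. If the later forms ask something else, the footnote is wrong.

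**Most of the cost is captured anyway.** Hospital care, probably the largest item and the main consequence of a recurrence, is recorded for the full year. This stands, and it confines the NHS consequence to primary and community care.

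**The bias is not shown.** A reader might infer that the 1-year incremental cost is biased towards non-operative treatment. That needs the uncovered weeks to be costed at zero, which the article nowhere says, and contact rates and unit costs by arm, which it does not give. The form and schedule are the same in both arms. With an even event rate, scaling each window up to its interval would recover the total at some loss of precision. The direction is plausible because of recurrence; the size is unknown. A reader might also carry the family items into cost per success, but the NHS perspective excludes them.

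**Short recall can be a deliberate choice, and costing rules belong in the Health Economics Analysis Plan.** Both are fair. The absence of a scaling or imputation rule from the article is not the point here. The point is a stated recall period that conflicts with the stated visit intervals and the stated completeness.

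**Conclusion.** The point holds in a limited form. Read literally, the CSRI observes 24 of 52 weeks and leaves 28 (about 26 to 31 across the visit windows) without primary and community care data for the 1-year cost-effectiveness analysis. That conflicts with the completeness of resource use data claimed for the visits. This rests on one assumption: that the 6-week recall applies at every administration, as the footnote's placement implies.

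The 61% of post-6-week time that is uncovered is a share of time. It becomes a share of contacts missed only if contacts are evenly spread, and it is not a share of cost. Under-counting, plausibly greater in the non-operative arm, would follow only if the gaps were treated as zero. It is worth correcting, but it does not threaten the trial's main conclusion.

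**What to change.** 1. Reconcile footnote 3 with the visit schedule. Keep 6 weeks at the first visit. At 4, 8 and 12 months ask about the time since the last trial visit, with its date filled in, and record which recall version was used. If the later forms already do this, correct the footnote and nothing else is needed.

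2. For calls already completed with 6-week recall, have the Health Economics Analysis Plan define the uncovered weeks as missing and scale or impute them by arm, allowing for recurrence or readmission in the gap. They should not be counted as zero. Simple scaling would use factors of about 11.4/6 = 1.9 at 4 months and 17.4/6 = 2.9 at 8 and 12 months. It assumes that the observed 6 weeks represent the whole interval, which is doubtful for a child whose recurrence fell in the gap.

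**Cost.** A wording change on the e-CSRI and one extra field. The price is more recall error over 11 to 17 weeks and mixed recall versions, since recruitment began in March 2022. The change can still help: with recruitment due to end around March 2026, 12-month calls would run to about March 2027.
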